#### Secondary outcomes

Difference in the regional response of BOLD contrast to pinprick nociceptive stimulation after duloxetine treatment (MRI2) between responder and non-responder groups.Functional connectivity differences post duloxetine treatment (MRI2) using network metrics of BOLD fMRI under resting condition between treatment responder and non-responder groups.Correlation between baseline CPM and TS with brain activity and connectivity changes from baseline to post 6 weeks of duloxetine treatment (rsfMRI and pinprick fMRI).Group differences in brain activity (pinprick fMRI and rsfMRI) and structure (T1-weighted brain MRI) in pain processing, limbic and modulatory pathways changes from baseline to following 6 weeks of duloxetine treatment, in comparison to placebo.Identification of baseline QST (CPM, TS, PPT) and questionnaire parameters (BDI, STAI, PCS, ICOAP) that predict response to duloxetine.Multivariate treatment response prediction model.

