The aim of this study is to investigate the neural mechanisms of pain relief in chronic OA pain following treatment with duloxetine and to establish multimodal brain signatures to predict treatment response. We will use a unique multimodal MRI design to identify key mechanisms and predictors of duloxetine-induced pain relief in chronic OA pain. This will include brain resting state functional connectivity, ASL, nociceptive functional (f)MRI, structural T1-weighted brain MRI, proton spectroscopy, quantitative sensory testing (QST) and questionnaire assessments.

We hypothesise that responding and non-responding patients with OA have different limbic signatures, differences in negative affect and sensory pain phenotypes. Additionally, we hypothesise that duloxetine induces functional brain changes in emotional regulatory networks.

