## Main hypotheses

Analgesic response to duloxetine treatment can be predicted using a range of baseline brain imaging markers and QST.Analgesic response to duloxetine is mediated by modulation of neural networks underpinning emotional control.Duloxetine-induced changes in brain activation differ between responders and non-responders.

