### Primary outcomes

#### Treatment mechanism

Change in the regional response of BOLD contrast to pinprick nociceptive stimulation after duloxetine treatment (MRI2) versus baseline (MRI1) in treatment responder group.Functional connectivity change from baseline (MRI1) to post duloxetine treatment (MRI2) using network metrics of BOLD fMRI under resting condition in treatment responder group.

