#### Response prediction

Differences in nociceptive BOLD response and network function at baseline between responders and non-responders.

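### Two secondary outcomes compare responders with non-responders on the post-treatment scan alone, so they cannot separate a differential change from a difference already present at baseline

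*Protocol article*

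**What the plan says.** All references are to the protocol article.

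- **Main hypotheses**, third hypothesis: "Duloxetine-induced changes in brain activation differ between responders and non-responders".
- **Secondary outcomes**, first: "Difference in the regional response of BOLD contrast to pinprick nociceptive stimulation after duloxetine treatment (MRI2) between responder and non-responder groups".
- **Secondary outcomes**, second: "Functional connectivity differences post duloxetine treatment (MRI2) using network metrics of BOLD fMRI under resting condition between treatment responder and non-responder groups".
- **Response prediction** (a primary outcome): "Differences in nociceptive BOLD response and network function at baseline between responders and non-responders". Background and rationale expects that "responding and non-responding patients with OA have different limbic signatures, differences in negative affect and sensory pain phenotypes", and the first main hypothesis is that "Analgesic response to duloxetine treatment can be predicted using a range of baseline brain imaging markers and QST".
- **Treatment mechanism** (primary): "Change in the regional response of BOLD contrast to pinprick nociceptive stimulation after duloxetine treatment (MRI2) versus baseline (MRI1) in treatment responder group". The companion connectivity outcome is likewise a change within responders.
- **Response definition**: a responder is a patient whose BPI severity falls by 50% between baseline and end of treatment, so membership is known only after treatment.
- **Data analysis**: the named higher-level tests are a paired t-test for treatment effects, a two-sample t-test of responders against non-responders at baseline, and correlations. The list is declared open-ended.

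**The concern.** The hypothesis concerns a difference in change, but the two outcomes closest to it measure a difference in level at one visit. In randomised groups that would matter little, because the expected baseline difference is zero. Responders and non-responders are not randomised groups. They are sorted by outcome, and a primary hypothesis of this trial is that they already differ at MRI1 in nociceptive BOLD response and network function.

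If that hypothesis is true and the difference is stable, the MRI2 contrast will tend to be positive even when duloxetine changes both groups equally. If the baseline difference runs opposite to the differential change, the MRI2 contrast can be null when the effect is real. At stake is the interpretation of the responder comparison, which is central to a mechanistic study.

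**Working it through.** **1. Does another stated outcome compare change between the two groups?**

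| Outcome | Uses MRI1 and MRI2? | Responders v non-responders? |
|---|---|---|
| Primary, treatment mechanism (both) | Yes | No, responders only |
| Primary, response prediction | No, MRI1 only | Yes |
| Secondary 1 and 2 | No, MRI2 only | Yes |
| Secondary 3 (correlation of CPM and TS with brain changes) | Yes | No |
| Secondary 4 (group differences in brain change) | Yes | Comparator named is placebo |

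No row clearly has both. A change shown in responders alone does not show that non-responders changed less. The article names the baseline scan or a change from baseline wherever it means change (both treatment mechanism outcomes, secondary 3 and 4), so its absence from secondary 1 and 2 does not look like shorthand.

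**2. The plan's own sizing (Sample size estimation).** Alpha is 0.05/10 = 0.005. With 19 evaluable per group, 19/0.9 = 21.1, rounded up to 22; 19/(0.9 × 0.8) = 26.4, rounded up to 27; 3 × 27 = 81. The stated target reproduces. No effect size is printed. For a one-sample, one-tailed t-test with n = 19, alpha 0.005 and 80% power, the noncentral t distribution (18 df, noncentrality d√19) gives d = 0.865. That value is in SDs of within-person change. It serves below only as the upper of three illustrative baseline differences.

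**3. MRI2-only test when the two groups change equally.** Assumptions: 19 per group; equal SDs; a baseline difference of d0 SD that persists in full; a two-sided two-sample t-test with 36 df. The noncentrality is d0 × √(19/2) = 3.082 × d0, and the critical values are 2.028 (0.05) and 2.990 (0.005).

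| d0 (assumed) | Noncentrality | Significant at 0.05 | Significant at 0.005 |
|---|---|---|---|
| 0.3 | 0.92 | 15% | 3% |
| 0.5 | 1.54 | 32% | 9% |
| 0.865 | 2.67 | 74% | 39% |

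**4. Comparison of change under the same conditions.** The baseline difference cancels in MRI2 minus MRI1. Simulation (20,000 runs per setting; within-person correlation r of 0.3, 0.5 and 0.7; d0 of 0, 0.5, 0.8 and 1.0) gave rejection rates of about 5% and 0.5%, as intended.

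**5. Masking.** With a baseline difference of −0.8 SD, a differential change of +0.8 SD and r = 0.5, the expected MRI2 difference is −0.8 + 0.8 = 0. The MRI2-only test rejects in 5% of trials at 0.05, and the change comparison in 67%.

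**6. Precision of a change score.** With equal SDs, the variance of MRI2 − MRI1 is 2(1 − r) times that of MRI2. It is smaller only if r > 0.5. For a true 0.8 SD difference, no baseline difference and r = 0.3, the change test has 53% power at 0.05 against 67% for MRI2 alone.

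**The case against.** The best case for the plan has four parts.

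- **An outcome definition is not a model.** A condensed article may leave baseline adjustment or an interaction to the analysis plan, and its list of tests is open. This is fair as far as it goes, but the point is not that a model is missing. The outcome as written fixes the visit, and that visit alone does not answer hypothesis 3.
- **The fourth secondary outcome is change-based.** The study works with three groups (placebo, responder, non-responder), so it might be meant to compare change across all three. That reading is possible, and a reader who concluded that hypothesis 3 goes entirely untested would go too far. But the only comparator named is placebo. Nor does the article tie the first two secondary outcomes to hypothesis 3; that link is inferred from their subject.
- **The baseline difference will be reported anyway**, because it is a primary outcome. Any carry-over should then be visible, so it is not certain that baseline differences will be mistaken for treatment effects. The risk remains, since showing two levels side by side is not a test of the difference in change.
- **The size is hypothetical.** This stands. The 74% is not an expected error rate for this trial: 0.865 comes from a one-sample test of change and is not a planned baseline effect.

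Two further inferences fail. If only part of a baseline difference persists, the groups really have changed differently, so a significant result is not a false positive: at 50% persistence of 0.865 SD, the change test itself rejects in 20%, 25% and 39% of trials at r = 0.3, 0.5 and 0.7. And leaving out MRI1 does not always lose precision against a raw change score, as step 6 shows.

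**Conclusion.** The point holds as a mismatch between hypothesis and outcome in two secondary outcomes. An MRI2-only difference between these outcome-defined groups cannot distinguish a pre-existing difference from a differential treatment change, and no stated outcome clearly makes the comparison of change.

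Under equal change and full persistence, the chance of a significant MRI2 difference runs from 15% to 74% at 0.05, and from 3% to 39% at 0.005, for assumed baseline differences of 0.3 to 0.865 SD with 19 per group. The article gives neither the baseline difference nor the within-person correlation, so these figures show how the contrast behaves and do not forecast the result. The primary outcomes do not depend on this contrast. It should be corrected because it bears on one of the three main hypotheses.

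**What to change.** Redefine both outcomes, pinprick BOLD and resting connectivity, as the difference between responders and non-responders in MRI2-minus-MRI1 change (the group-by-visit interaction). Report the MRI1 difference beside each, and keep MRI2-only differences as description.

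The cost is a change of wording in two secondary outcomes; both scans are already scheduled. The downside is that a raw change score is less precise than MRI2 alone if the within-person correlation is below 0.5. The change contrast removes a stable baseline difference but does not make the groups randomised, so the report should say so. A matching responder contrast within the placebo arm is not recommended: it would split about 19 evaluable participants, and response is defined only for duloxetine.

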### Other outcomes

Exploratory outcomes include, but are not limited to, determination of gene variations that can be linked with duloxetine treatment response and gamma-aminobutyric acid (GABA) modulation according to changes in pain severity. Imaging data from the baseline study may be pooled with other studies undertaken in the Nottingham Arthritis Research Pain Centre ARUKPC if the participants consent to this.

### Data analysis

Clinical, QST and psychometric data will be compared between groups and conditions using the latest versions of statistical and image analysis software including SPSS (version 21.0).

Brain imaging data will be analysed using the latest versions of several established toolboxes: FSL (FMRIB Software Library),^28^ PyMVPA (Multivariate Pattern Analysis),^29^ Statistical Parametric Mapping V.8 (London, UK), REST (Resting-State fMRI Data Analysis Toolkit), Brain Connectivity Toolbox and GRETNA (Graph Theoretical Network Analysis)^30–32^ and LCModel (Linear Combination Model) for MRS data.^33^ All data will undergo established quality control and standard recommended preprocessing. Preprocessing steps for functional data include motion correction, slice-timing correction using Fourier-space time-series phase-shifting, non-brain tissue removal, spatial coregistration to T1-weighted image and normalisation to the MNI anatomical standard space. Spatial smoothing will be carried out using an isotropic Gaussian kernel and a high-pass temporal filtering will be applied. Next, for task-related fMRI, statistical maps will be generated for contrasts of interest, such as to identify brain activity evoked by pinprick in each individual scan using first-level general linear model.

Z-scores will be extracted from regions of interest of pain processing nodes defined from meta-analysis,^7^ emotion regulatory, default mode and salience network including anterior cingulate cortex, anterior insula, amygdala, brain stem and thalamus for both task-related and resting functional maps. Individual functional connectivity maps will be also generated. These will be used on higher level analysis which will include, among others: (1) Paired t-test to evaluate treatment effects; (2) two-sample t-test to compare groups (responders and non-responders) at baseline; (3) correlation analysis to determine associations with psychometric and QST measurements.

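### For pinprick fMRI the group tests use z-scores from single-scan models, so a difference in scan noise between visits or groups can mimic or hide a difference in BOLD response.

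*Protocol article*

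**What the plan says.** The Data analysis section of the protocol article describes one chain for the pinprick task.

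- A general linear model is fitted to each scan: "statistical maps will be generated for contrasts of interest, such as to identify brain activity evoked by pinprick in each individual scan".
- A summary is then taken per region: "Z-scores will be extracted from regions of interest of pain processing nodes", located by meta-analysis, and from further named networks, "for both task-related and resting functional maps".
- After a sentence on individual connectivity maps, the section continues: "These will be used on higher level analysis which will include, among others: (1) Paired t-test to evaluate treatment effects". It then lists a "two-sample t-test to compare groups (responders and non-responders) at baseline" and correlations with psychometric and QST measures.

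No contrast estimate or percent signal change is named as the value taken forward.

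The primary outcomes are worded as response. Under Treatment mechanism the outcome is "Change in the regional response of BOLD contrast to pinprick nociceptive stimulation" from MRI1 to MRI2 in responders. Under Response prediction it is the baseline difference in nociceptive BOLD response (and network function) between responders and non-responders.

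**The concern.** A z-score from a single-scan model is a signal-to-noise ratio. Two scans with the same BOLD response give different z-scores if residual error differs, for example through head movement or physiological noise. The outcome asks how large the response is; the extracted value also reflects how clean the scan was.

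Two primary comparisons are exposed, by different routes.

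- **Paired test in responders.** This is a within-group comparison of MRI2 with MRI1, so no placebo arm removes a shift in noise between visits. Responders are defined by a 50% fall in pain, so it is plausible, though not documented, that they lie stiller at MRI2.
- **Baseline two-sample test.** This would be biased only if responders and non-responders already differed in scan noise before treatment.

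A noise difference can be reported as a drug mechanism or a predictor, and a real attenuation of the response can be cancelled by cleaner scans at MRI2.

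**Working it through.** **Inputs from the document.** Sample size estimation: about 19 evaluable participants per group, a one-sample one-tailed t-test, 80% power, and alpha 0.005 to allow for 10 tests. The chain reproduces: 0.05/10 = 0.005; 19/(0.9 × 0.8) = 26.4, rounded up to 27 per group; 3 × 27 = 81. The present point does not change these figures. The document gives no z-value, standard error, motion or noise figure, so everything below on noise is assumed.

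**Formula.** z = b/SE, where b is the contrast estimate for a region and SE its standard error in that scan. If b is unchanged and SE is multiplied by f, the mean z is divided by f.

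**Setting A: noise falls at MRI2.** Assumed: mean effect 0.5, between-person SD 0.25, session SD 0.15, typical SE 0.15 with log-SD 0.2, n = 19 pairs, no true change, 20,000 simulated trials.

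- Mean z at MRI1: 0.5/0.15 = 3.33; variation in SE multiplies this by exp(0.2²/2) = 1.02, giving about 3.4.
- With f = 0.8 the mean z at MRI2 is 3.4/0.8 = 4.25, a rise of 0.85 with no change in response.

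Rejection by the paired t-test, two-sided:

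| Noise at MRI2 | z-scores, 0.005 | z-scores, 0.05 | Contrast estimates, 0.005 |
|---|---|---|---|
| unchanged | 0.4% | about nominal | about 0.5% |
| 10% lower | 1.4% | 9% | about 0.5% |
| 15% lower | 2.9% | 17% | about 0.5% |
| 20% lower | 6.1% | 28% | about 0.5% |

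Repeat runs agree to within simulation error (1.2%, 2.9% and 6.2% at 0.005).

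The same setting, one-tailed at 0.005:

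- Test for a decrease: 0.41%, 0.08%, 0.02% and 0% for noise unchanged, 10%, 15% and 20% lower.
- Test for an increase: about 10% for noise 20% lower.

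**Setting B: noise rises at MRI2, or is higher in one group.** Assumed: between-person SD of the effect equal to one SE, mean z of 1 to 3 and n = 19 (per group in the two-sample case). The test is one-tailed at 0.005, in the direction in which z falls. A 20% higher SE lowers a mean z of 2 to 2/1.2 = 1.67, and of 3 to 3/1.2 = 2.5. Rejection with no true change:

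| Mean z | SE +10% | SE +20% | SE +30% |
|---|---|---|---|
| 1 (paired) | 1.0% | 1.8% | 2.8% |
| 2 (paired) | 1.8% | 4.8% | 9.4% |
| 3 (paired) | 3.2% | 11.1% | 23.8% |

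For the two-sample test, rejection is 3.3% (mean z 2, SE 20% higher in one group) and 13.5% (mean z 3, SE 30% higher). Contrast estimates stay at about 0.4% to 0.6% throughout.

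Both settings vary residual noise only. Contrast estimates hold their level here because nothing in the model scales the BOLD signal itself.

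**The case against.** **Direction.** Less movement at MRI2 lowers noise and raises z. The sample size rests on a one-tailed test, with an effect taken from the anterior cingulate in a healthy-volunteer duloxetine study that the Background describes as showing attenuated activity. Tested for a decrease, cleaner scans at MRI2 make the z-score test conservative: the harm is lost power, not a false finding. This stands. A reader might infer that z-scores simply inflate false positives; the documents do not support that, because they state neither the direction of the test nor that of any noise change.

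**Baseline comparison.** A reader might also infer that drug effects on physiology, or noise at MRI2, could produce the responder versus non-responder difference. They cannot in the listed two-sample test, which uses scans taken before any drug. Only a pre-existing noise difference could, and nothing in the article points to one.

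**Safeguards and size.** The plan has motion correction, quality control and a 10% allowance for unusable scans, and the secondary comparison with placebo would offset noise shifts common to both arms. These reduce the risk but do not equalise residual error between usable scans, and the placebo comparison is not the primary test. It is fair that every noise figure above is assumed.

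**Wording.** One phrase covers task and resting maps, the pronoun carrying values forward follows a sentence on connectivity maps, and the list of analyses is open-ended: "These will be used on higher level analysis which will include, among others". For resting data, z-scores may mean Fisher-transformed correlations, which are not an estimate over its standard error, so the point does not extend there. For the pinprick task, no reading of the text puts contrast estimates into the regional tests. A full imaging plan might do so, but the article states a specific choice rather than leaving the matter open.

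**The remedy.** Contrast estimates and percent signal change are not immune to drug effects that scale the BOLD signal. This stands as a limit on the fix.

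**Conclusion.** The point holds for pinprick fMRI. The article specifies a noise-dependent quantity for outcomes defined as response, and a systematic difference in residual noise would bias the paired test in responders or the baseline group test, either way.

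The size is conditional on assumed noise. At n = 19 with a mean z of about 3.4, noise 10% to 20% lower at MRI2 takes the two-sided error at 0.005 from 0.5% to about 1% to 6%. One-tailed with 20% lower noise, it is about 10% for an increase and near 0% for a decrease. With equal noise there is no inflation. The documents do not show that noise differs between visits or groups in this trial. The change is worth making because the exposure affects primary analyses and is cheap to remove.

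**What to change.** Replace the sentence on extraction with one that separates the two modalities, for example:

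> For pinprick fMRI, the mean contrast parameter estimate (or percent signal change) in each predefined region, from the model fitted to each scan, will be used in the paired, two-sample and correlation analyses. For resting connectivity, Fisher-transformed correlations will be used.

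Add that motion and residual noise will be reported by visit and by group, so that a reader can judge whether they differed. Z-scores for the task may still be shown descriptively.

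State the limitation alongside: this removes sensitivity to residual noise, but not to drug effects that scale the BOLD signal itself. Neither the secondary placebo comparison nor the ASL data corrects for those automatically.

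The cost is a few sentences. The estimates come from the same model run, so no new data, participants or change in sample size are needed. The change should be fixed before the blind is broken for analysis.

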### Sample size estimation

The sample size calculation was performed according to the guidelines stated by Lenth and colleagues.^34^ Estimates of change in functional activation were deduced from a duloxetine intervention study (effect size was calculated based on p values provided for the ACC).^17^ Using the Java applets,^35^ it was estimated that a one-sample, one-tailed, t-test would have 80% power at alpha of <0.005 (to allow for 10 multiple independent tests) with approximately 19 participants per group: responders to duloxetine treatment, non-responders and placebo groups.

Based on previous experience of non-usable imaging data due to patient and/or technical factors in 10% of cases, a sample size of >22 participants per group was necessary. A further allowance for 20% dropout gives 27 participants in each group, resulting in a recruitment target of 81 participants. The study is not be powered to assess clinical efficacy.

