## Background and rationale

Osteoarthritis (OA) is a major cause of long-term disability and chronic pain in the adult population. Knee and hip OA combined ranked 11th in a recent survey of global burden of disease, and symptomatic knee OA is several folds more common than hip OA.^1^ Current treatment options consist of a combination of pharmacological and non-pharmacological alternatives.^2^ Despite these options, around 20% of patients do not get satisfactory pain relief, even after undergoing joint replacement surgery.^3^ This strongly supports the notion that chronic osteoarthritis pain has a strong central component.^4–6^

Application of advanced neuroimaging tools led to novel understanding of central mechanisms underpinning acute and chronic pain states.^7^ Functional imaging in particular lends itself to the mechanistic study of analgesic treatment.^5 8–10^ Neuroimaging may also prove useful in guiding mechanism-based personalised therapy.^10–12^

To comprehensively describe brain activation states across regions and functional properties, the concept of so-called brain ‘signatures’ has emerged that can be derived from regional and network analysis of blood-oxygen-level dependent (BOLD) functional MRI data at rest or during controlled stimulation, or from cerebral blood flow maps based on arterial spin labelling (ASL) techniques.^13 14^

Duloxetine, a serotonin and norepinephrine reuptake inhibitor, has antidepressant and anxiolytic properties and is currently also used to treat chronic pain conditions. However, the precise mechanisms by which this drug acts to relieve pain are unclear and only around 50% of patients with OA have sufficient pain relief after duloxetine intake^15^; currently there is no way to predict responders.^15 16^ In healthy participants, duloxetine was found to attenuate activity in affect processing areas (amygdala, thalamus, insula and anterior cingulate cortex) while simultaneously increasing functional coupling between the amygdala and the anterior insula during an emotional face matching task.^17^ Duloxetine in major depression augmented connectivity in the anterior default mode network,^18^ while reduced connectivity within the subgenual cingulate was predictive of clinical antidepressant response.^18^

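### The 80% power is stated for a one-tailed test, but the primary mechanism outcomes name no direction; two-tailed at 0.005, 19 responders give about 71% to 75%

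*Protocol article*

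**What the plan says.** Under Sample size estimation, the protocol article reports that "it was estimated that a one-sample, one-tailed, t-test would have 80% power at alpha of <0.005 (to allow for 10 multiple independent tests". The number this requires is given as about 19 in each of three sets of patients: those who respond to duloxetine, those who do not, and the placebo arm. It does not print the effect size, saying only that "effect size was calculated based on p values provided for the ACC" in a published duloxetine study. It then allows for "non-usable imaging data due to patient and/or technical factors in 10% of cases" and continues: "A further allowance for 20% dropout gives 27 participants in each group, resulting in a recruitment target of 81 participants".

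The first primary mechanism outcome is the within-responder change in the BOLD response to pinprick. The second is "Functional connectivity change from baseline (MRI1) to post duloxetine treatment (MRI2) using network metrics of BOLD fMRI under resting condition in treatment responder group". Neither says whether a rise or a fall is expected. The Primary objectives, the Main hypotheses and the closing paragraph on aims also speak of change, modulation or difference without a sign. Data analysis lists "Paired t-test to evaluate treatment effects" and does not give its sidedness.

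Background and rationale does report signs. In healthy participants duloxetine lowered activity in several affect-processing areas, including the anterior cingulate cortex (ACC), "while simultaneously increasing functional coupling between the amygdala and the anterior insula". In major depression it raised connectivity in the anterior default mode network.

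**The concern.** For a within-responder change, a one-sample (paired) formula is the right design. The question is its sidedness. A one-tailed test is justified when the direction of the effect is fixed beforehand, and here the powered test has a direction while the outcomes do not.

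Two things are at stake. If the paired tests are run two-tailed at 0.005, as undirected outcomes would suggest, the stated 80% does not apply to them. If they are run one-tailed in one common direction, a change of the other sign cannot be declared in either primary mechanism outcome, although the background gives reason to expect a fall in activation and a rise in connectivity. Either way, a reader cannot tell what power the primary imaging comparisons have.

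**Working it through.** **Inputs from Sample size estimation.** One-sample t-test, one-tailed, alpha 0.005, power 80%, n about 19 evaluable per group, 10% unusable scans, 20% dropout, 27 recruited per group.

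**Formula.** For a one-sample or paired t-test with standardised change d, the test statistic follows a noncentral t with n − 1 degrees of freedom and noncentrality d√n. Power is the probability that it exceeds the critical value t(1 − α) for one tail, or t(1 − α/2) for two tails. The opposite tail is negligible here.

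**Step 1: the plan's own figures.**
- Alpha: 0.05/10 = 0.005, as stated.
- Inflation: 19/0.9 = 21.1, then 21.1/0.8 = 26.4, rounded up to 27; 3 × 27 = 81, as stated.
- Power: the 80% cannot be reproduced independently because d is not printed, so d is back-solved. With n = 19 and a one-tailed critical value of 2.878 (18 df), 80% power needs a noncentrality of 3.770, so d = 3.770/√19 = 0.865. If 19 is a rounded-up number, d could be as large as the value that gives exactly 80% at n = 18, which is 0.894.

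The printed calculation is therefore consistent with d of about 0.865 to 0.894.

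**Step 2: the same effect, two-tailed at 0.005, n = 19.** The critical value rises to 3.197.

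| d | Noncentrality d√19 | Two-tailed power |
|---|---|---|
| 0.865 | 3.770 | 70.8% |
| 0.894 | 3.898 | 74.5% |

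The shortfall against 80% is 80 − 74.5 = 5.5 to 80 − 70.8 = 9.2 percentage points.

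**Step 3: what 80% two-tailed would take.**
- At n = 19, d must be 0.94.
- At d = 0.865, n = 20 gives 74.4%, n = 21 gives 77.7% and n = 22 gives 80.6%.
- At d = 0.894, n = 20 gives 78.0% and n = 21 gives 81.1%.

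So 21 to 22 evaluable responders would be needed.

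**Step 4: is there slack in recruitment?** On the plan's own allowances, 27 × 0.8 × 0.9 = 19.4 evaluable per group, which leaves no reserve.

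**Step 5: directions, side by side.**

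| Item | Direction in the protocol article |
|---|---|
| Powered test (Sample size estimation) | One tail, sign not named |
| Primary outcome: pinprick BOLD change | None stated |
| Primary outcome: resting connectivity change | None stated |
| Main hypotheses | None stated |
| Planned paired t-test (Data analysis) | Sidedness not stated |
| Background: regional activation, including ACC | Decrease |
| Background: amygdala–insula coupling, default mode connectivity | Increase |

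**The case against.** The strongest reply is that nothing in the calculation is wrong. It names a one-tailed test, its alpha and inflation check, and no passage commits to a two-tailed analysis, so there is no direct contradiction. The power was derived for functional activation in the ACC, where the background gives one direction only, a decrease. For connectivity, the reported effects of duloxetine are both increases. One tail per measure, activation down and connectivity up, would be coherent, and a full protocol or analysis plan might say so.

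Much of this stands. A reader might infer that the background shows both signs for the same measure. It does not: the signs differ between activation and connectivity, not within either. A reader might also call this an arithmetic error, and it is not one. What remains is that the article fixes a one-tailed test for its power claim, words the primary outcomes without direction, and declares no direction for any region or metric. The per-measure reading is possible but written nowhere.

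A further inference would be that the error rate is inflated. If the tail were chosen after seeing the data, each test would run at 0.01, and ten independent tests would give 1 − 0.99^10 = 9.6% instead of 1 − 0.995^10 = 4.9%. No passage plans or suggests such a choice, so this is not a finding against the protocol.

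Finally, the gap corresponds to two or three responders, and with lower losses than assumed it would close: at 10% dropout, 27 × 0.9 × 0.9 = 21.9 would be evaluable. That is fair as to size, but the plan's own allowances give 19.4.

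**Conclusion.** The concern holds as a mismatch between the powered test and the outcomes. The 80% applies to a one-tailed paired test whose direction is never named. For an undirected, two-tailed paired test at 0.005 with 19 evaluable responders, power is about 71% to 75%.

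This rests on three assumptions: d is back-solved because it is not printed; the same d applies to both primary mechanism outcomes; and 19 responders are evaluable, which itself depends on about half of the duloxetine arm responding. Quoting 71% alone would be too precise, since it is the lower end of the range, but the whole range lies below 80%. The point concerns only the within-responder mechanism outcomes.

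**What to change.** In Data analysis, state that the primary paired t-tests are two-tailed at 0.005. In Sample size estimation, restate the power for the mechanism outcomes as about 71% to 75% with 19 evaluable responders or, equivalently, a detectable change of about 0.94 SD at 80% power, and print the effect size used. Keep a one-tailed test only for a region or network metric whose expected direction is named before the data are analysed.

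The cost is a sentence in each section and a less favourable stated power. No extra patients are needed and study conduct does not change.
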